#### ***Urgent notification of other relevant safety information***

Urgent notification to AEMPS (Área de ensayos clínicos de la Subdirección Gral. De Medicamentos de Uso Humano), will also be employed for all the information that could modify the risk-to-

benefit balance of the experimental therapy or advice changes in the therapy, or in the trial.

Regulatory authorities will be notified of the new information will be notified as soon as possible and no later than 15 days from when the investigator has knowledge of it. Additional information will be provided also as soon as possible.

### ***Annual safety report***

All SUSAR and SAEs reported will be notified to the AEMPS and the CEIm in an annual safety report.

## **10. STATISTICAL ANALYSIS**

The statistical analysis will be carried out in accordance with the principles specified in the International Conference on Harmonization (ICH) Topic E9 (CPMP / ICH / 363/96). A detailed Statistical Analysis Plan (SAP) agreed upon by the CT Executive Board and the Project Statistician will be available early during the recruitment phase. This SAP will follow the general regulatory recommendations given in the ICH E9 guidance, as well as other specific guidance on methodological and statistical issues. Also, it will stick to the recommendations given by the consensus documents of the scientific journals to improve reliability and value of medical research literature by promoting transparent and accurate reporting of clinical research studies.

The SAS System^5 (Release 9.4, or an upgraded version), or equivalent validated statistical software, will be the statistical software used to analyse the data sets.

A summary of the overall approach to statistical analysis is presented hereafter.

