### ***Expected duration of the Trial***

Expected recruitment will take 2 months since first site initial visit, which will follow the approval of the AEMPS.

Each patient will participate in the trial for a maximum of 29 days, including a screening phase of 1 day, treatment duration of 1-2 day, initial follow-up and a follow-up visit at 28 days from randomisation.

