##### *Objectives and endpoints*

Table 1 - Objectives and endpoints

| OBJECTIVES                                                                                                                                                                     | ENDPOINTS AND OUTCOME MEASURES                                                                                                                                                                 |
|--------------------------------------------------------------------------------------------------------------------------------------------------------------------------------|------------------------------------------------------------------------------------------------------------------------------------------------------------------------------------------------|
| PRIMARY                                                                                                                                                                 |                                                                                                                                                                                                |
| Evaluate the efficacy of an early intervention with sarilumab in COVID-19 infected patients with pneumonia and regular oxygen supplement requirements (Brescia-COVID 1) | The primary endpoint is the proportion of patients progressing to severe respiratory failure (Brescia-COVID $\geq 2$ ), ICU admission or death from randomization up to day 15th of follow-up. |
| SECONDARY                                                                                                                                                               |                                                                                                                                                                                                |

---

**Evaluate effects of efficacy of an early intervention with sarilumab on secondary efficacy endpoints as compared to standard of care as assessed by:**

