### **Packaging and Labeling**

All study drugs will be administered as open label. No blinding methods will be used in this trial.

Experimental drugs will be supplied to pharmacies packaged and labeled according to the standard requirements for clinical trials. Sarilumab will be labelled with the study protocol code, batch number, content, expiry date, storage conditions, investigator and sponsor name. The study medication will be labelled in accordance with annex 13 of the European Good Manufacturing

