#### *Efficacy assessments: follow up visits*

Clinical follow-up visits will be performed at 3, 5, and 15 days after treatment randomisation. Patients in SOC group without sarilumab progressing to severe respiratory failure fulfilling criteria for treatment with anti-IL6 inhibitors according to clinical practice guidelines, as defined by the presence of Brescia-COVID 2-3 plus inflammatory markers, will be rescued with sarilumab at the same doses and be included in an open-label phase. This group of patients will be followed up by two additional weeks after receiving sarilumab as rescue medication (days 3, 5 and 15 following sarilumab administration).

Patients randomly assigned to sarilumab therapy at baseline progressing to Brescia-COVID 2-3 will be rescued according to local clinical practice protocols.

For all patients a final follow-up visit is planned at D28 from randomization, regardless of the initial treatment assigned.

The following outcomes should be assessed:

- Hospitalization.
- ICU admission
- Hospital discharge
- Oxygen requirements.
  - Oxygen mask with reservoir bag.

- Non-invasive mechanical ventilation (via mask) or high flow oxygen nasal tubes
  - Mechanical ventilator requirement (via endotracheal tube or tracheostomy tub).
  - ECMO requirement.
- Ordinal scale score:
  1. Not hospitalized, no limitations on activities.
  2. Not hospitalized, limitation on activities.
  3. Hospitalized, not requiring supplemental oxygen.
  4. Hospitalized, requiring supplemental oxygen.
  5. Hospitalized, on non-invasive ventilation or high flow oxygen devices or oxygen mask with reservoir bag.
  6. Hospitalized, on invasive mechanical ventilation or ECMO.
  7. Death.
- PaO2/FiO2 Index or SpO2/FiO2 Index.
- Temperature °C
- Chest radiography (at least one during the follow-up period, recommended between D3-5, unless medically indicated any other day as part of the routine care)
- Laboratory disease parameters (CRP, d-dimer, IL-6, LDH, lymphocyte counts, ferritin, plus any routing laboratory determinations usually performed by the patients's physicians)
- Death.
- Concomitant medications
- Brescia-COVID score

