## **Study outcomes**

### *Primary Endpoint*

The primary endpoint is the proportion of patients progressing to severe respiratory failure (Brescia-COVID  $\geq 2$ ), ICU admission, or death.

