### ***Primary endpoint***

The primary endpoint is the proportion of patients progressing to severe respiratory failure (Brescia-COVID  $\geq 2$ ), ICU admission, or death. The proportion of patients with failure at day 7, will be estimated using a log-binomial regression model including stratification variables. In the unexpected event that the model does not fit, the Poisson regression model with long-link and robust variance estimator will be used instead.

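### The SAP may be agreed after recruitment starts in an open-label trial with unrestricted interim looks, while the protocol still gives two different primary time points

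*Protocol*

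**What the plan says.** **Timing of the plan.** The opening of Section 10 says that a detailed plan, agreed between the trial's executive board and the project statistician, "will be available early during the recruitment phase". The section on expected duration adds: "Expected recruitment will take 2 months since first site initial visit".

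**Blinding and looks at the data.** Section 7, Packaging and Labeling: "All study drugs will be administered as open label. No blinding methods will be used in this trial". Section 8, Calendar of Evaluation of Trial Variables, lets the principal investigator carry out an interim analysis at a time of their choosing, with patients still in follow-up. Section 11 lists interim results among the reasons for stopping early. No section requires the plan to be signed before such a look.

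**Primary time point.** Table 1 (Objectives and endpoints) counts "ICU admission or death from randomization up to day 15th of follow-up". The primary endpoint paragraph in Section 10 says: "The proportion of patients with failure at day 7, will be estimated using a log-binomial regression model including stratification variables". The synopsis and Section 8 define the endpoint without a time point; Section 8 begins "The primary endpoint is the proportion of patients progressing to severe respiratory failure" and gives no day. Visits do not match day 7 either: "Clinical follow-up visits will be performed at 3, 5, and 15 days after treatment randomisation".

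**The concern.** A plan finished after the first patient enters is not a fault in itself. It is weaker here because three things coincide. Treatment is known from the first patient. Accumulating data may be analysed at any time. And the protocol contains two candidate windows for its primary analysis.

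Whoever writes the plan must choose between day 7 and day 15, and either choice can be defended by pointing at a protocol section. If the choice is made after outcomes have been summarised by arm, the test no longer holds its nominal two-sided 5% level. Even if the choice was made innocently, a reader of the final report has no assurance of that from the protocol.

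**Working it through.** **1. The plan's own figure.** Section 10 assumes 25% versus 10%, two-sided 5%, 80% power and 1:1 allocation. The pooled rate is 0.175.

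n per arm = [1.960 × √(2 × 0.175 × 0.825) + 0.842 × √(0.25 × 0.75 + 0.10 × 0.90)]² / 0.15² = (1.053 + 0.443)² / 0.0225 ≈ 99.5, rounded up to 100.

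The stated 100 per arm is reproduced, and the timing of the plan does not affect it. The 25% and 10% carry no time point, so the sample size paragraph does not settle the window.

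**2. How much could be visible, and when.** Inputs: 200 patients (Section 10) and 2 months of recruitment (Section 2), taken as 61 days. Assumption: uniform accrual from day 0.

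Rate = 200 / 61 = 3.28 per day. Randomised by day t = 3.28t; past day 7 = 3.28(t − 7); past day 15 = 3.28(t − 15), with negative values set to zero.

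| Recruitment day | Randomised | Past day 7 | Past day 15 |
|---|---|---|---|
| 14 | 46 | 23 (11% of 200) | 0 |
| 21 | 69 | 46 (23%) | 20 (10%) |

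Taking 2 months as 60 days changes these counts by at most one patient. Slower accrual at the start, which is plausible because the 2 months run from the first site's initial visit, would lower them.

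**3. What a late choice of window could do.** This is an illustration by simulation under no treatment effect. Assumptions: 100 per arm; 25% event rate in both arms; 40%, 60% or 80% of events by day 7; pooled two-sample test at nominal 5%; window chosen as the one with the larger standardised difference among patients already seen, with both windows complete for them.

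| Patients seen when choosing | Type I error | Recruitment day on which that many are past day 15 |
|---|---|---|
| 24 | 5.4–5.7% | 15 + 24/3.28 ≈ 22 |
| 50 | 5.8–6.5% | 15 + 50/3.28 ≈ 30 |
| 100 | 6.7–7.7% | 15 + 100/3.28 ≈ 45 |
| all 200 | 7.3–9.0% | after follow-up ends |

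With the window fixed in advance, the same simulation gives 4.9–5.2%. A choice made about three weeks into recruitment therefore costs less than one percentage point. The cost grows the longer the conflict stays open.

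**The case against.** The strongest reply is that the protocol already fixes most of the primary analysis: a log-binomial model with stratification variables, a Poisson fallback, the analysis populations, and missing binary outcomes counted as failures. Exclusions from populations are to be decided independently of the randomisation codes before data lock. Deviations from the planned analysis go in the final report. A dated plan could later be compared with accrual dates. The trial describes itself as exploratory phase II. All of this stands, and it means that a pre-recruitment plan is not the only safeguard.

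None of it covers the time point. The review without randomisation codes concerns population membership only. The deviation clause would not catch a choice between day 7 and day 15, because either conforms to one part of the protocol.

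A reader might infer more than the documents support:
- *That the plan's authors will have seen results by arm.* No section says so. It is only possible, given open-label treatment and the unrestricted interim clause.
- *That about a quarter of the primary data would be exposed.* That holds only for a day-7 window at recruitment day 21. For day 15 it is 10% then, and zero at day 14.
- *That the timing breaches ICH E9.* Section 10 invokes the guideline, but its text is not available here.
- *That other open details are further conflicts*, such as the bracketed stratification of the log-rank test and Cox model, or which method applies to marker changes. These concern secondary endpoints and are commonly left to the plan.

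**Conclusion.** The point holds in a limited form. The protocol allows its primary time point to be settled after by-arm outcomes have been summarised, and no provision prevents this. It does not show that this will happen.

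If the plan is agreed within about three weeks of the start, at most about 23% of patients would be past day 7 and 10% past day 15, under uniform accrual over 61 days. The illustrated inflation at a similar amount of data is under one percentage point. It could approach 8% if half the outcomes were seen before the choice, under the simulation's assumptions. The documents do not date the plan more closely than early in recruitment, so the true size cannot be fixed. The distortion is probably small, but it is avoidable at almost no cost.

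**What to change.** 1. In the opening of Section 10, replace the timing phrase with a commitment such as: *The SAP will be signed and dated before the first patient is randomised.* If recruitment has already begun: *The SAP will be signed and dated before any tabulation or interim analysis by arm, and the number of patients who had reached the primary outcome at signing will be recorded.*
2. Reconcile day 7 and day 15 in the protocol itself. Carry one time point through the synopsis, Table 1, the primary endpoint in Section 8 and the analysis paragraph in Section 10, check it against the visit schedule, and state to which window the 25% and 10% refer.

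The first change moves statistician work forward by a few weeks. The second is an editorial amendment. The change in timing does not affect patients, visits or the sample size.

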### ***Sample size estimation***

To obtain a power of 80.00% to detect differences in the contrast of the null hypothesis  $H_0: p_1 = p_2$  by means of a bilateral Chi square test for two independent samples, taking into account that the level of significance is 5.00%, and assuming that the proportion in the Reference group is 25.00%, the proportion in the Experimental group is 10.00%, and that the proportion of experimental units in the Reference group with respect to the total is 50.00 % it will be necessary to include 100 experimental units in the Reference group and 100 units in the Experimental group, totalling 200 experimental units in the study.

### ***Data Review (DR)***

The Data Review (DR) will be performed before lock of database. Data will be examined for compliance with the trial protocol by the monitor and the data manager. Deviations will be sent to the project statistician to plan listings for the Data Review (DR). The objective is to carry out the population selection and definition of the final study populations as well as a preliminary assessment of the quality of the trial data.

---

 CPMP/ICH/363/96. ICH E9 Statistical Principles for Clinical Trials. URL: [http://www.ema.europa.eu/ema/pages/includes/document/open\\_document.jsp?webContentId=WC500002928](http://www.ema.europa.eu/ema/pages/includes/document/open_document.jsp?webContentId=WC500002928), last access: 20-Mar-2020.

 EMEA Scientific Guidelines for Human Medicinal Products, Clinical Efficacy and Safety Guidelines, General Guidelines. URL: <https://www.ema.europa.eu/en/human-regulatory/research-development/scientific-guidelines/clinical-efficacy-safety/biostatistics>, last access: 20-Mar-2020.

 EQUATOR-network (Enhancing the Quality and Transparency of Health Research). URL: <http://www.equator-network.org/resource-centre/library-of-health-research-reporting/>, last access 20-Mar-2020

 SAS version 9.4 software, SAS Institute Inc., Cary, NC, URL: <http://www.sas.com/>, last access: 20-Mar-2020

## ***Analysis populations***

There will be the following analysis populations for this study:

1. Full Analysis Set (FAS): All patients who are randomized into the study will be included in the FAS population.
2. Per Protocol Population: Per protocol (PP) patient sets will be defined as those patients included in the FAS set without major protocol deviations that might impact the study's main assessments. These deviations will be assessed during the data review prior to database lock.
3. The Safety population is defined as all randomized participants who received the investigational product.

The precise reasons for excluding participants from each population will be fully defined and documented independently of the randomization codes during the data blinder review and before data lock.

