|                                                |                                                                                                                                                                                                                                                                                                                                                                                                                                                                                                                                                                                                                                                                                                                                                                                                                                                                                                                                                                                                                                                                                                                                          |
| Investigational product                 | SRLmb is a recombinant human immunoglobulin (IgG) 1 monoclonal antibody that binds specifically to both soluble and membrane-bound interleukin-6 (IL-6) receptors (sIL-6R $\alpha$ and mIL-6R $\alpha$ ) and inhibits IL-6-mediated signaling. It is approved for the treatment of moderate to severe rheumatoid arthritis. The recommended dose of Sarilumab is 200 mg once every 2 weeks administered as a subcutaneous injection.                                                                                                                                                                                                                                                                                                                                                                                                                                                                                                                                                                                                                                                                                                     |

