**To evaluate safety of sarilumab as compared to SOC**

Safety through day 29

- Cumulative incidence of serious adverse events (SAEs)
- Cumulative incidence of Grade 3 and 4 adverse events (AEs).

Serious adverse events (SAEs).  
Grade 3 or 4 Adverse events (AEs).

|                                                                                                                                                   |                                                                                                                                    |
|---------------------------------------------------------------------------------------------------------------------------------------------------|------------------------------------------------------------------------------------------------------------------------------------|
| To evaluate differences in the effect of sarilumab on the serum levels of inflammatory cytokines in patients infected with COVID-19.       | Changes in serum level of CRP, IL-6, lymphocyte count, neutrophils count, d-dimer, LDH, ferritin, coagulation tests                |
| To evaluate differences in the proportion of patients showing more than >1 organ failure, e.g. cardiovascular, liver and kidney failure | Patients showing more than >1 organ failure through day 15                                                                         |
| To identify prognosis factors of sarilumab efficacy related to laboratory parameters or disease features                                   | Focused medical history, demographic characteristics, COVID-19 history, concomitant medication, and laboratory disease parameters. |

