of the primary analysis and be rescued according to local treatment protocols, which may include tocilizumab. Patients in the control group (SOC group without sarilumab) progressing to Brescia-COVID 2-3 plus inflammatory markers, will be given the option to be rescued with sarilumab at the same doses and, in that case, be included in an open-label phase and be followed up for two additional weeks (with visits at 3, 7 and 15 days after sarilumab rescue administration).

A final follow-up visit will be conducted for all patients at D29 from randomization, regardless of initial treatment assignment.

Figure 1 – Graphical study design

[figure not shown]

Figure 2 – Graphical study design OPEN-LABEL PHASE

[figure not shown]

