### ***Dosing and Administration***

Experimental group: Patients in the treatment arm will receive sarilumab plus corticosteroids on top of SOC medication. Sarilumab will be administered intravenously as a single dose following this posology:

- Patients <75kg body weight: single 200mg SARILUMAB dose (1 single-dose pre-filled syringe containing 200 mg sarilumab in 1.14 ml solution (175 mg/ml) added to 100 mL 0.9% sodium chloride for a 1-hour intravenous infusion).
- Patients ≥75kg body weight: single 400mg SARILUMAB dose (2 single-dose pre-filled syringes, each containing 200 mg sarilumab in 1.14 ml solution (175 mg/ml) added to 100 mL 0.9% sodium chloride for a 1-hour intravenous infusion).
- Corticosteroids will be administered intravenously following this posology: Methylprednisolone 1mg/kg/day (or corticosteroid dose equivalents) for at least 3 days

**Control group:** Patients in the control group will receive corticosteroids on top of SOC medication.

Corticosteroid: will be administered intravenously following this posology: Methylprednisolone 1mg/kg/day (or corticosteroid dose equivalents).

SOC: All patients will continue background SOC according to local clinical practice protocols and be followed up until disease progression, patient withdrawal, ICU admission, hospital discharge, loss of follow up, or death.

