### ***Prohibited Concomitant Therapies***

The following medications are prohibited while receiving protocol therapy:

- Concomitant administration of tocilizumab.
- Any investigational agents other than sarilumab.
- Concurrent use of live vaccines.
- Other immunomodulators or immunosuppressant medications.

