- Adverse events: Adverse events (AEs), serious AEs, and laboratory abnormalities from the signature of the informed consent form or oral consent documentation, where appropriate. At inclusion they will be collected from the beginning of sarilumab administration. AEs will be documented as per the National Cancer Institute's Common Terminology Criteria for Adverse Events (CTCAE) version 5.0 (Appendix 4).

If the patient has been discharged, they will be contacted by phone. If possible, a visit will be scheduled to complete the evaluation.

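### As worded, the Safety population admits only patients who received sarilumab, so it holds no unexposed comparator for the planned safety comparison with standard of care

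*Protocol*

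**What the plan says.** The definition appears under Analysis populations in Section 10 and again, in the same words, under Subject included in each analysis: "The Safety population is defined as all randomized participants who received the investigational product".

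Three other places fix what that means:

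- The synopsis row for the investigational product describes only sarilumab: "SRLmb is a recombinant human immunoglobulin (IgG) 1 monoclonal antibody that binds specifically".
- Prohibited Concomitant Therapies (Section 7) bars "Any investigational agents other than sarilumab", which treats sarilumab as the sole investigational agent.
- Dosing and Administration (Section 7) gives controls no sarilumab and no placebo: "Patients in the control group will receive corticosteroids on top of SOC medication".

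Controls have one route to sarilumab. For those who progress to a Brescia-COVID score of 2 or 3 with inflammatory markers, Section 5 states that they "will be given the option to be rescued with sarilumab at the same doses and, in that case, be included in an open-label phase".

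Against this, the safety objective in Table 1 (Section 4) is comparative: "To evaluate safety of sarilumab as compared to SOC". Section 10 then plans a descriptive comparison of safety endpoints by arm, includes adverse events in the inferential analyses, and sends binary safety outcomes to the regression model used for the primary endpoint.

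**The concern.** A safety comparison needs patients from both arms. This definition admits patients by exposure to the test drug, and in a trial without placebo only one arm receives that drug by design. The controls who do enter have progressed first, which is a component of the primary endpoint, and have then been given sarilumab. They are neither a random sample of the control arm nor unexposed to the drug.

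Safety is in the trial's title and is a stated secondary objective. If the definition is followed, the tables for the Safety population cannot show how adverse events on sarilumab compare with those on SOC. If it is not followed, someone has to choose another set during an open-label trial, possibly with results by arm in view.

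**Working it through.** **Inputs (Section 10, Sample size estimation).** Control event rate 25%, experimental event rate 10%, two-sided 5% chi-square test, 80% power, 1:1 allocation, 100 patients per arm.

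**Step 1. Reproduce the plan's figure.** With pooled variance under the null and no continuity correction:

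n per arm = [1.960 × √(2 × 0.175 × 0.825) + 0.842 × √(0.25 × 0.75 + 0.10 × 0.90)]² / 0.15²
= (1.053 + 0.443)² / 0.0225, which rounds up to 100.

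Power at 100 per arm is 80.2%. The stated size reproduces, so 100 controls and a 25% event rate are sound planning inputs for the count below.

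**Step 2. Count who meets the definition.** Assume that all 100 patients in the sarilumab arm are dosed. Let s be the share of control failures who receive sarilumab as rescue. The protocol does not give s, so it is varied.

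Controls in the set = 100 × 0.25 × s

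| s (assumed) | Controls in the set | Total in the set | Controls left out |
|---|---|---|---|
| 0 | 0 | 100 | 100 |
| 0.5 | 12.5 | 112.5 | 87.5 |
| 1 | 25 | 125 | 75 |

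Three features of the protocol push s below 1. Section 5 makes sarilumab rescue optional, and it says that local rescue may use tocilizumab. The 25% also covers the whole composite, including ICU admission and death, whereas rescue requires a Brescia-COVID score of 2 or 3 plus inflammatory markers. Section 8 states the rescue without calling it optional, which would push s up. If only doses in the randomised phase count as receipt, s is 0.

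**Step 3. Vary the event rate.** With s = 1, a control event rate of 15% gives 15 controls in the set and a rate of 35% gives 35. The figure of 25 is an expectation under the planning rate and not a limit.

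**Step 4. Count unexposed patients.** For every value of s and every event rate, the number of patients in the set without sarilumab exposure is 0, because exposure is the entry condition. This is the central result, and it depends on no assumption about rescue.

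**Step 5. Compare with a set based on any study treatment.** If receipt of either regimen qualifies, the set holds up to 100 + 100 = 200 patients and the between-arm comparison can be made.

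**The case against.** The strongest reply is that nothing is lost. No sentence says that the safety comparison must run on the Safety population. Table 2 schedules adverse event reporting from baseline to the day 28 visit without distinguishing arms, the calendar of evaluations collects events for 28 days, and the FAS contains every randomised patient. The intention to compare arms is plain, and this is an exploratory phase II trial whose primary efficacy analysis is untouched.

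Much of this stands. A reader might infer that the comparison is impossible or that control data are discarded, and the documents do not support that. What remains is that the protocol names a Safety population, defines it twice in a way that conflicts with its own safety objective, and never assigns safety analyses to the FAS. This is a stated definition and not a detail left to the SAP. A SAP that follows it inherits the conflict, and one that departs from it contradicts the protocol.

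A second reply is that the investigational product could include the corticosteroids given to everyone. The synopsis row and the list of prohibited therapies do not support that reading.

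Two further inferences are tempting and go too far:

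- **That sarilumab would look safer than it is.** This requires rescued controls to stay in the control column. The protocol does not say whether the set is analysed as randomised or as treated. Analysed as treated, the rescued progressors would join the sarilumab group and could make its profile look worse, with no comparator left.
- **That controls have no start for adverse event collection.** Section 8 does say "At inclusion they will be collected from the beginning of sarilumab administration", but the sentence before it starts collection at consent, which applies to both arms. In Registry of AE (Section 9), the 15-day limit counted from the first sarilumab dose concerns how long an event is followed, and it stands beside criteria that do not depend on arm. The wording is inconsistent, but controls do have a start and an end.

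**Conclusion.** The definition is wrong as written. It yields a Safety population of about 100 sarilumab-arm patients and 0 to 25 of 100 controls, none of them unexposed to sarilumab, and it contradicts the planned safety comparison with SOC. The absence of an unexposed comparator follows from the wording alone. The count of controls rests on the 25% planning rate, on full dosing in the sarilumab arm and on an assumed share of failures rescued with sarilumab.

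The comparison remains recoverable from data already scheduled in both arms. No direction of bias is established, and 25 should not be read as an upper bound. The point still needs correction, because the conflict is in the protocol itself, nothing else in the protocol repairs it, and the change is small.

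**What to change.** 1. In both places in Section 10, define the Safety population as all randomised patients who received any study treatment, meaning sarilumab plus corticosteroid plus SOC, or corticosteroid plus SOC. Analyse it by the treatment initially received. Entry should rest on receiving either regimen and not on receiving the assigned one, so that a patient given the other arm's regimen stays in the set and is counted under what was given.
2. Report events after sarilumab rescue in controls separately from events before it.
3. Reconcile the wording tied to sarilumab dosing in Section 8 (Efficacy assessments) and Section 9 (Registry of AE) with the consent start and the 28-day collection, so that both arms have the same start and end. Collection already begins at consent, so the start should not be moved later to randomisation.

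The cost is wording in four places. It needs no new data and leaves the sample size, the treatments and the primary analysis unchanged.
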